#### Inclusion and exclusion criteria

Participants with FRDA are eligible for TRACK-FA if they meet the inclusion and exclusion criteria as outlined in Table 1. Due to the nature of this criteria, this study is only targeting those individuals with FRDA that are largely ambulant and in the first 25 years of disease duration.

**Table 1 pone.0269649.t001:** Inclusion and exclusion criteria used for the enrolment of FA participants into the TRACK-FA study.

Inclusion criteria below	Exclusion criteria below
Age ≥ 5 years	Acute or ongoing medical or other conditions not attributed to FRDA
Biallelic GAA repeat length > 55 in intron 1 of *FXN* and/or GAA repeat length > 55 in intron 1 of *FXN* in one allele and another type of mutation that is inferred to cause loss of function in the second *FXN* allele	Other neurological condition apart from FRDA
Age of disease onset ≤ 25 years	MR contraindications (e.g., pacemaker or other metallic surgical implants)
Disease duration ≤ 25 years	Presence of metallic dental braces (creates unwanted artifacts)
Written informed consent provided	Pregnancy
*FARS functional stating score of ≤ 5 and a total mFARS score of ≤65 on enrolment	

*FARS, Friedreich’s Ataxia Rating Scale; mFARS, Modified Friedreich’s’ Ataxia Rating Scale.

Control participants must meet the following criteria: age > 5 years and be able to provide written informed consent. Control participants will be excluded if they have any MR contraindications, are pregnant, or present with any diagnosed medical and neurological condition which may interfere with the conduction of the study.

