### Study design

The TRACK-FA study will involve the participation of children and adults with genetically confirmed FRDA and control participants. Participants will be allocated to one of four groups based on their age: ≥ 18 years, 11–17 years, 8–10 years, and 5–7 years. Control participants will be matched at the cohort level to the FRDA participants for age, sex, handedness, and years of education. A recruitment ratio of 1:1 (FRDA: control) will be used for those aged 5–10 years and a 2:1 ratio (FRDA: control) will be used for participants ≥ 11 years of age.

We aim to recruit a total of 200 individuals with FRDA and 104 control participants across seven testing sites. This number was informed by a power analysis (see below) and necessitated a multi-site collaborative network to achieve this goal. All participants will then be assessed at three visits [Visit 1 (V1), Visit 2 (V2), Visit 3 (V3)] with identical assessments; each visit will take place approximately 12 months apart and no more than two months before or after the 12-month interval.

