### Status and timeline of the study

TRACK-FA participant recruitment will occur throughout the period of January 2021 to October 2022. As of September 2021, total of a total of 27 individuals with FRDA consisting of 21 adult participants with FRDA, five older paediatric participants with FRDA and 1 younger paediatric participant with FRDA, have been tested. A total of 11 control participants have been tested.

The target recruitment statistics for the 18-month period will include a total of 200 participants with FRDA, including 110 adult participants with FRDA, 82 participants with FRDA of age 11–17 and eight total participants of age 5–10 (Fig 2).

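### Metallic dental braces bar FRDA participants from enrolment because of image artifact, but the control criteria omit them, so artifact at baseline can differ by diagnosis

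*Protocol article*

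**What the plan says.** The section on inclusion and exclusion criteria in the protocol article gives two sets of rules.

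- **FRDA participants.** Table 1 is captioned "Inclusion and exclusion criteria used for the enrolment of FA participants into the TRACK-FA study". Its exclusions include "MR contraindications (e.g., pacemaker or other metallic surgical implants" and, in a row of its own, "Presence of metallic dental braces (creates unwanted artifacts". The reason given for the braces row is image quality, not safety.
- **Controls.** The text below the table reads "Control participants will be excluded if they have any MR contraindications, are pregnant, or present with any diagnosed medical and neurological condition", the last being limited to conditions that may interfere with the study. Braces are not named.

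No other section extends the braces criterion to controls. Under Study design, "Control participants will be matched at the cohort level to the FRDA participants for age, sex, handedness, and years of education". Nothing in that list would balance dental hardware between the groups.

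Both groups have the same brain and cervical cord imaging for their age. Participants over 10 years have the full protocol, including diffusion, QSM and spectroscopy.

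**The concern.** The study compares imaging measures between two groups. The stated reason for excluding braces applies to a control's scan as much as to a patient's. An image-quality criterion applied at entry to one group only lets measurement error, and possibly bias, differ by diagnosis at the first visit.

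The controls are the reference for the baseline comparison (Analysis of cross-sectional differences at baseline), which runs across all age groups and is meant to show differences between children and adults. They are also the reference for the slope difference (Assessing the longitudinal changes over time) and for the 12-month comparison (Difference-in-difference analyses). Adolescents, in whom one would expect most of the braces, make up a large part of the control group.

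The safeguards described do not clearly close the gap. Monthly phantom testing cannot detect metal in a participant. The independent quality control covers one third of subjects, and only brain anatomical and diffusion data. The article states no rule for scans affected by braces.

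**Working it through.** **1. Is a control with braces eligible as written?** Table 1 gives MR contraindications and braces separate rows, with pacemakers and metallic surgical implants as examples of the former. Braces are therefore not listed as an MR contraindication. The control sentence carries over MR contraindications and pregnancy, and it omits braces. The term it uses does not clearly cover them.

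**2. How many controls are exposed?** The FRDA targets (Status and timeline of the study) are 110 adults and "82 participants with FRDA of age 11–17 and eight total participants of age 5–10". Under Study design, "a 2:1 ratio (FRDA: control) will be used for participants ≥ 11 years of age"; the youngest children are recruited one to one. The implied number of controls is

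110/2 + 82/2 + 8/1 = 55 + 41 + 8 = 104,

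which reproduces the stated target of 104. So 41 of 104 controls (39%) are aged 11–17.

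**3. How far could the control mean move at one visit?** The documents give neither the prevalence of braces nor the size of the artifact. Assume a share *p* of controls aged 11–17 with braces, and a shift of *s* SD in the same direction in each of them. The mean in that band then moves by *p* × *s*.

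| *p* | controls affected (41 × *p*) | *s* = 0.25 | *s* = 0.5 | *s* = 1.0 |
|---|---|---|---|---|
| 5% | 2.1 | 0.0125 | 0.025 | 0.05 |
| 10% | 4.1 | 0.025 | 0.05 | 0.10 |
| 20% | 8.2 | 0.05 | 0.10 | 0.20 |
| 30% | 12.3 | 0.075 | 0.15 | 0.30 |

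Pooled over the 55 + 41 = 96 controls aged 11 or over, with no braces among adults, the extremes shrink to 0.0125 × 41/96 = 0.005 SD and 0.30 × 41/96 = 0.13 SD.

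**4. What would that do to a baseline test within the band?** For 82 FRDA participants against 41 controls, SE = √(1/82 + 1/41) = 0.191 SD. With no true difference and a bias of *b*, the two-sided 5% test rejects with probability 1 − Φ(1.96 − *b*/SE) + Φ(−1.96 − *b*/SE):

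| *b* (SD) | false-positive rate |
|---|---|
| 0.0125 | 5.0% |
| 0.05 | 5.8% |
| 0.10 | 8.2% |
| 0.20 | 18% |
| 0.30 | 35% |

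**5. What reaches the change analyses?** Table 1 governs enrolment only.

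- Braces worn at every visit largely cancel in a within-person slope or difference.
- Braces fitted after the first visit can occur in either group.
- Braces present at the first visit and removed later are the route that the criteria open for controls alone. The share of controls affected in this way cannot be estimated from the documents, so no slope bias is computed.

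**The case against.** The strongest reply is that this is a condensed article. The FRDA criteria have a full table and the controls two sentences. A fuller protocol may list braces for controls, or sites may treat braces as an MR contraindication. That may be how the study is run, in which case the sponsor need only say so. It does not remove the inconsistency: the article states both sets of criteria, and they differ on a point whose reason applies equally to both groups.

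Three stronger readings are tempting, and the documents do not support them.

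- A reader might infer that artifact can enter control images only. Nothing in Table 1 restricts braces after enrolment, so an FRDA adolescent fitted with braces later would still be scanned.
- A reader might infer that the reference slope is distorted for every longitudinal comparison. Only removal of braces present at the first visit differs by group under the criteria, and the article does not say which outcome measures braces affect.
- A reader might set a shift of up to 0.30 SD against the planned d = 0.3. That effect is defined under Sample size calculation for change over 24 months. The shift here is in a mean at one visit, so the two should not be compared directly.

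It is also fair to say that both inputs to the size are assumed and that the calculation takes every shift to be in the same direction. Artifact of mixed sign would add noise more than bias.

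**Conclusion.** The point holds as an asymmetry in the enrolment criteria. As written, braces exclude an FRDA participant and do not exclude a control, which permits differential artifact in the baseline comparison, chiefly at ages 11–17. The effect on change is confined to a narrower route. The size is unknown: it runs from nothing of consequence to a bias that would matter for a baseline comparison within the adolescent band, depending on a prevalence and a shift that the documents do not give. No sample-size or power figure changes. The criterion should be corrected because it is cheap to do so, not because harm has been shown.

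**What to change.** 1. Add the presence of metallic dental braces to the control exclusion criteria, so that the enrolment criterion is identical in both groups. If it already applies to controls, state that.
2. Record brace status for every participant at each visit. The article's list of medical and demographic information has no dental item.
3. For braces present at the second or third visit, apply the same image-quality rule to both groups, and run a sensitivity analysis without the affected scans. Do not exclude those participants automatically: that would lose follow-up data in both groups, on top of the 20% attrition already planned for.
4. Flag any control already scanned with braces for the same sensitivity analysis, where brace status can be established. As of September 2021 only 11 controls had been tested.

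The cost is one line in the criteria, one data item per visit, and a slightly smaller pool of adolescent controls.

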**Fig 1 pone.0269649.g001:**
[figure not shown]
Summary of TRACK-FA study procedures according to participant age. The testing schedule varies according to age. All participants will also undergo a speech assessment, whilst all FRDA participants will undergo additional clinical testing.

*Collection of medical and demographic information*. Medical history specific to FRDA will be taken in the enrolment session for all participants with FRDA. The following information will be collected: the length of *FXN* GAA repeat expansions on the smaller (GAA1) and larger (GAA2) allele, the type of mutation detected, age of symptom onset including first symptom, disease duration, presence of diabetes and medical information pertaining to nervous system disorders (apart from FRDA), heart conditions, vision impairments, skeletal abnormalities (scoliosis and foot deformities), hearing conditions, bowel and bladder conditions, presence of inflammatory diseases, details on concurrent trial participation and COVID-19 status.

The following information will be collected for all participants: height and weight (used to calculate body mass index (BMI), and medications (prescription/non-prescription).

*MRI scanning to assess primary outcomes*. All participants will undergo brain and (cervical) spinal cord imaging procedures lying supine in a three tesla (3T) MRI scanner (Siemens Skyra, Siemens Prisma or Philips Ingenia). Significant effort has been made to ensure harmonisation of MR protocols across all the sites with vigorous testing of the imaging sequences prior to the commencement of the study. The inclusion of QSM, diffusion MRI and MRS in the procedure allows for the quantification of iron accumulation, microstructural and neurochemical profile of areas pertinent to disease pathology [39], potentially providing further insights into neuronal damage and gliosis associated with the neurodegenerative nature of this disease [32].

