#### Analysis of cross-sectional differences at baseline

Individuals with FRDA and control groups will be compared at baseline using adjusted and unadjusted analyses. For unadjusted analyses, the two groups will be compared using the two-sample Student’s t-test or using the Mann-Whitney U-test for those variables that exhibit substantial skewness or otherwise do not match the assumptions of the two-sample t-test. For adjusted analysis a linear modelling approach will be used to predict case/control status, with demographic variables and site effects as covariates. This analysis will be conducted across all age groups represented in the study design, further enabling the possibility to observe differences in biomarkers between children and adults with FRDA and matched control participants. The baseline analysis provides the starting point from which functions such as rate of change can be derived for each of the parameters.

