#### Assessing the longitudinal changes over time

The within-person longitudinal slopes across the multiple visits will be estimated using a mixed linear model in which the slope for each participant is treated as a random effect. Within this framework we will assess the significance of a fixed effect that captures the difference in mean slope for individuals with FRDA with respect to controls. Due to the participant demographic in this study the analysis of within person slopes can give an indication of how age of onset and disease stage/severity can influence the subsequent clinical changes that occur within the parameters of participant demography.

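### Any other neurological condition excludes an FRDA participant, but a control is excluded only if the condition may interfere with running the study, so controls with outcome-relevant neurological disease can be admitted

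*Protocol article*

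**What the plan says.** The section Inclusion and exclusion criteria prints a rule for each group. In Table 1, a person with FRDA is excluded for "Other neurological condition apart from FRDA" and for "Acute or ongoing medical or other conditions not attributed to FRDA". Neither entry carries a further condition. Below the table, a control is excluded for MR contraindications, for pregnancy, or if they "present with any diagnosed medical and neurological condition which may interfere with the conduction of the study".

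Three other places bear on whether the difference is made good later:

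- Study design: "Control participants will be matched at the cohort level to the FRDA participants for age, sex, handedness, and years of education". Health status is not a matching variable.
- Collection of medical and demographic information: "Medical history specific to FRDA will be taken in the enrolment session for all participants with FRDA". For everyone, controls included, "The following information will be collected for all participants: height and weight", followed by medications.
- Analysis of cross-sectional differences at baseline: the adjusted comparison is made "with demographic variables and site effects as covariates". The main longitudinal test is of a "fixed effect that captures the difference in mean slope for individuals with FRDA with respect to controls".

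**The concern.** The control group is the reference for the baseline comparison, the slope comparison and the 12-month difference-in-difference comparison. For a clean reading, the groups should differ by FRDA and not also by how they were screened for other brain disease.

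The FRDA rule turns on whether another neurological condition exists. The control rule turns on whether a condition gets in the way of the study. A control with a stable neurological condition could lie through the scan, complete the tests and give blood, and so pass, while an FRDA participant with the same condition would not. If that condition affects brain volume, diffusion measures, cord area or cognition, it becomes part of the reference value. The qualifier is also loose enough for seven sites to draw the line in different places.

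**Working it through.** **1. What each rule lets through, read as written**

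| Condition | FRDA participant | Control |
|---|---|---|
| Other neurological, hinders procedures | excluded | excluded |
| Other neurological, affects outcomes but not procedures | excluded | eligible |
| Medical, not attributed to FRDA, does not hinder procedures | excluded if acute or ongoing | eligible |
| Medical, attributed to FRDA in cases (the Introduction lists diabetes and cardiomyopathy) | eligible | eligible unless it may interfere |

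The second row is the clear mismatch. The third is also a mismatch. The fourth shows that full parity on medical conditions is not available, because cases keep FRDA-related comorbidity.

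**2. How many controls this concerns**

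FRDA targets (Status and timeline of the study): 110 adults, 82 aged 11–17, 8 aged 5–10. Ratios (Study design): 2:1 from age 11, 1:1 below. Controls = 110/2 + 82/2 + 8/1 = 55 + 41 + 8 = 104, which reproduces the stated target. By September 2021, 11 controls had been tested, leaving 104 − 11 = 93 to come.

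**3. Baseline level: form of the effect**

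Let a share f of controls be shifted by s standard deviations (SD) on an outcome. Then

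- shift in control mean = f × s
- control variance = 1 + f(1 − f)s²

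The documents give neither f nor s. The values below are assumptions that show only the form:

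| f | s = 0.3 | s = 0.5 | s = 1.0 |
|---|---|---|---|
| 5% | 0.015 SD | 0.025 SD | 0.05 SD |
| 10% | 0.03 SD | 0.05 SD | 0.10 SD |
| 20% | 0.06 SD | 0.10 SD | 0.20 SD |

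A shift toward FRDA values narrows the contrast by this amount. A shift away widens it by the same amount. If conditions act in both directions, the mean shifts tend to cancel and mainly variance is added. In the most extreme cell, f = 20% and s = 1.0, the control SD rises from 1 to √(1 + 0.2 × 0.8 × 1) = 1.08.

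**4. Change over time**

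If a condition shifts a person's level by a constant c at every visit, the 12-month change is (Y12 + c) − (Y0 + c) = Y12 − Y0. The constant drops out, and it drops out of a within-person slope in the same way. Only a condition that alters the rate of change moves the slope or difference-in-difference contrast. Baseline comparisons are therefore more exposed.

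**5. Sites**

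Adjustment for potential site differences examines sites among controls alone. With 104/7, about 15 controls per site if spread evenly (an assumption), two affected controls at one site and none elsewhere would move that site's mean by 2/15 × s, or 0.04 to 0.13 SD for s from 0.3 to 1.0. The standard error of a mean of 15 is 1/√15 = 0.26 SD. Uneven screening could thus contribute to an apparent site difference, but on these assumptions it would seldom produce one alone.

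**6. Planning figures**

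Sample size calculation rests on d = 0.3 for change over 24 months. No figure in it depends on control health, and none changes under the fix.

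**The case against.** The strongest reply is that the threshold is low. A condition need only be one that may interfere, and in a neuroimaging study a site could well count brain disease as interfering. This stands to the extent that the text does not prove affected controls will be enrolled. The defect is a loose, non-parallel criterion. But if parity depends on seven sites choosing the broad reading, the protocol has not fixed it.

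A second reply is that an article condenses the full protocol. That covers missing definitions and forms. It does not cover two printed rules that differ.

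A third is that the controls are young. On the targets above, 41 + 8 = 49 of 104 (47%) are under 18. Onset by 25 and duration up to 25 years cap FRDA age near 50, and controls are matched on age. Relevant disease may be uncommon. This stands.

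A reader might also infer more than the documents support:

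- *That the FRDA–control contrast must shrink.* The sign depends on which way a condition moves each outcome, which is not stated.
- *That the loss can be expressed as a fraction of d = 0.3.* That effect size is for 24-month change. A shift in baseline level is in different units and largely cancels from change.
- *That the imbalance can never be adjusted for.* Medications are recorded for all participants, and Study visits lists medical information at each visit. These are partial proxies, though the baseline analysis names no health covariate.
- *That recording other nervous system disorders in FRDA participants contradicts Table 1.* Asking at enrolment may simply be how the exclusion is checked.
- *That the wide FRDA rule is costing recruitment.* COVID-19 impact attributes the delay to the pandemic, and nothing shows that Table 1 turned anyone away.

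**Conclusion.** The point holds as a stated difference between two eligibility rules. Other neurological disease is an unconditional exclusion in FRDA participants and a conditional one in controls, and the condition attached concerns study conduct, not the outcomes. Read as written, it can admit controls whose neurological disease affects brain, cord or cognitive measures, and it invites different practice across seven sites. Matching and the named baseline covariates do not correct for this.

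Its size cannot be determined from the documents. The possible consequences are bias in either direction, added variance, and spurious site differences among controls, with baseline comparisons more exposed than slopes. The conclusion rests on the literal wording. If every site already applies the broad reading, the practical effect is nil and only the wording needs repair. The case for acting is that this is an avoidable weakness in the FRDA–control contrasts and is cheap to remove.

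**What to change.** 1. Exclude controls for any diagnosed neurological condition, matching the FRDA rule (any other than FRDA).
2. State the remaining medical exclusion for both groups in the same terms: conditions likely to affect the study outcomes or completion of the visit, with FRDA-attributed conditions still allowed in cases. How far this should reach for controls is debatable, because cases retain their FRDA-related comorbidity. The neurological rule is the firm part.
3. For controls already enrolled, record neurological history at the next visit, and run a sensitivity analysis of the FRDA–control comparisons without those who fail the common rule.

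Cost: a wording amendment to Table 1 and the control criteria, a short history item for controls, and one sensitivity analysis. A few control volunteers become ineligible. With 11 of 104 controls tested by September 2021, few at that date would have needed retrospective checking. The sample size does not change.
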